#### **Interventions**

#### **Explanation for the choice of comparators {6b}**

Treatment as usual (TAU): Local NGOs will provide the course of intervention that they deem appropriate. No specific instructions will be given as to what TAU should entail, except not including elements specific to METRA. TAU will be documented ensuring understanding of the duration, frequency and type of treatment administered.

### **Intervention description {11a}**

METRA: Module 1: Memory specificity training ([name] et al., 2018; Moradi et al., 2014; Neshat-Doost et al., 2013; Raes et al., 2009; Martens et al., 2019) is a manualized training delivered over five 60-minute sessions to groups of 6-8 adolescents. MEST aims to enhance memory specificity through practice. Session 1 provides psycho-education about mental health and memory.

Participants practice recalling memories in response to positive and neutral cues, with support from the group facilitator. Attention is paid to the contextual, spatio-temporal and sensory-perceptual details of the memories (Raes et al., 2009). Participants' responses are discussed in the group. At the end of the session, homework exercises are introduced; for 10 cues (positive and neutral) participants need to generate a specific memory and are instructed to write down a 'specific memory of the day' every evening of the coming week (Raes et al., 2009). Session 2 starts with a brief summary of Session 1, the homework exercises are discussed and the Session then follows the same format as Session 1, with further practice focusing on recalling memories in response to positive and neutral cues. At the end of Session 2, the homework is explained; participants need to generate two different specific memories for 10 cues (positive and neutral) and write down two different 'specific memories of the day' every evening of the coming week (Raes et al., 2009). Session 3 is very similar to Session 2. However, in Session 3, participants also need to work with negative cues. The homework exercises are similar to those outlined in Session 2, but now also include negative cues. Session 4 involves further exercises using negative and ('counterpart') positive cues. It is also explained how overgeneral thinking can be addressed by recalling a single specific experience and examples are discussed to promote metacognitive awareness of when participants are starting to shift to unspecific thinking or more general retrieval (Raes et al., 2009). Session 5 includes further practice and a summary of Module 1. Module 1 focuses on everyday remembering.

Module 2: Writing for Recovery is a written exposure training involves five sessions (Kalantari et al., 2012; Sloan et al., 2018). In the first session the purpose of Module 2 is outlined. In the following sessions, the facilitator simply reads the instructions and the participant completes the writing task; writing about their trauma including thoughts and feelings. After 30 minutes, the facilitator instructs the participants to stop writing ([CHANGE 4: Timing of sessions reduced due to](#)

security concerns).

### **Criteria for discontinuing or modifying allocated interventions {11b}**

Discontinue trial if participants report significant distress or a significant proportion of participants report significant increase in symptomatology. This will be based on the reports and observations of the facilitators and decisions to continue/discontinue will be made by the trial monitoring body.

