#### **Eligibility criteria {10}**

Afghan refugee/returnee/war-affected adolescent girls aged 10-19 years with elevated psychological distress. This age range aligns with our pilot work and definitions of 'adolescent' (UNICEF, 2019b; WHO, 2019). As in our pilot studies, elevated psychological distress is defined as >30 on the Persian Child Revised Impact of Event Scale-13 (Child Outcomes Research Consortium, 2019) and/or >12 on the Persian Mood and Feeling Questionnaire – Short form (Neshat-Doost et al., 2006). Participants will be recruited in Kabul. Exclusion Criteria: a) high levels of suicidality, b) unmanaged psychosis/manic episodes in past month, and c) presence of head trauma/organic brain damage.

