#### **Assignment of interventions: allocation**

#### **Sequence generation {16a}**

After eligibility is confirmed and baseline data collected, participants will be randomly assigned in a 2:1 ratio to METRA or TAU ([CHANGE 5: Change in random assignment ratio approach due to resource and ethical reasons](#)). We have adopted an unequal randomization approach for resource and ethical reasons to maximize the number of participants in the treatment arm. This decision was made because following the change of government, there was increased insecurity and most international agencies withdrew from Afghanistan. Thus, there are now very few youth health interventions available that can be considered TAU. This unequal randomization approach has been employed in previous trauma-focused RCTs (including those conducted in LMICS) (Bass et al., 2016; Rae Olmsted et al., 2020) and the decision should not impact power for our statistical tests nor changed the scientific rigor of the study (Torgerson & Torgerson, 2008).

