**Interim analyses {21b}**

Not applicable

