## **Oversight and monitoring**

### **Composition of the coordinating centre and trial steering committee {5d}**

The Trial Steering Committee will provide overall supervision of the project. It will include independent members who will monitor trial progress, functioning of the partnership and ensure local and community involvement.

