### **Composition of the data monitoring committee, its role and reporting structure {21a}**

Not applicable

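### The stop rule in {11b} rests on facilitators' impressions, in effect of the METRA arm, and leaves out the blinded scores collected in both arms after each module

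*Supplement*

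**What the plan says.** All references are to protocol Version 2 (September 2021).

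- **Stop rule, {11b}.** The trial stops if participants report significant distress, or if "a significant proportion of participants report significant increase in symptomatology". No scale, size of change, proportion or time point is given. The evidence and the decider are set in one sentence: "This will be based on the reports and observations of the facilitators and decisions to continue/discontinue will be made by the trial monitoring body". The trial monitoring body is not defined elsewhere.
- **Who facilitates.** Facilitators appear in the METRA intervention description ({11a}), in the adherence section ({11c}) and in the blinding section ({17a}), where they are blind to hypotheses but not to allocation. For TAU, "Local NGOs will provide the course of intervention that they deem appropriate" ({6b}). What is recorded about TAU is its duration, frequency and type.
- **Scores.** Assessors blind to allocation collect all measures face to face in both arms at baseline, post-Module 1 and post-Module 2 ({8}, {17a}, {18a}).
- **Oversight.** Interim analyses ({21b}) and a data monitoring committee ({21a}) are marked not applicable. Of the Trial Steering Committee, {5d} says: "It will include independent members who will monitor trial progress, functioning of the partnership". It receives a monthly list of adverse effects, and serious ones are reported within one business day ({22}). No rise in score is defined as an adverse effect, and no tabulation by arm is mentioned.
- **Setting.** The change to 2:1 allocation is explained by events in the country: "following the change of government, there was increased insecurity and most international agencies withdrew from Afghanistan" ({16a}).

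**The concern.** The participants are distressed girls aged 10 to 19, and Module 2 asks them to write about their trauma. A rule that protects them must tell worsening caused by METRA from worsening caused by events around them. Randomisation supplies the means, because TAU girls live through the same period. The rule as written does not use it: its stated evidence comes from people who know they are delivering METRA and have no described contact with the TAU arm.

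The error can go either way. Background deterioration could be read as harm and stop a harmless trial. A rise that METRA does cause could be put down to the insecurity, and the trial would continue. The blinded scores that bear on the question exist at the right times, including just before Module 2, but the plan does not route them to whoever decides.

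**Working it through.** The stop rule states no figure, so there is none to reproduce. The calculation asks what a one-arm view can and cannot show.

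**Inputs**
- Allocation 2:1 ({16a}) and a target above 100 ({14}). Taking 100: 100 × 2/3 ≈ 67 METRA and 33 TAU.
- Pre-post correlation ρ: not in the plan. Assumed 0.5, range 0.3 to 0.7.
- A girl counts as risen if her score is more than 1 baseline SD above baseline. This cut is assumed.

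**Formula.** With normal scores of equal SD and a mean worsening of b SD, P(risen) = 1 − Φ((1 − b)/√(2(1 − ρ))). At ρ = 0.5 the denominator is 1:
- b = 0: 1 − Φ(1.0) = 0.159
- b = 0.3: 1 − Φ(0.7) = 0.242
- b = 0.5: 1 − Φ(0.5) = 0.309
- b = 0.8: 1 − Φ(0.2) = 0.421

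**Two situations that look the same from the METRA arm**

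| Situation | METRA risen | TAU risen | Difference |
|---|---|---|---|
| Background worsening 0.5 SD in both arms, METRA harmless | 67 × 0.309 = 20.7 (31%) | 33 × 0.309 = 10.2 (31%) | 0 |
| No background worsening, METRA harm 0.5 SD | 67 × 0.309 = 20.7 (31%) | 33 × 0.159 = 5.2 (16%) | 15 points |

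At ρ = 0.3 the shares for b = 0.5 and b = 0 are 33.6% and 19.9%; at ρ = 0.7 they are 25.9% and 9.8%. The gap is therefore 14 to 16 points across the range.

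**No cut on the METRA arm alone removes this.** A cut at 25% of METRA girls (17 of 67) is met with probability 0.87 in both situations. A cut at 35% (24 of 67) is met with probability 0.23 in both. Neither cut is in the plan; they only show that moving the cut changes how often a rule fires, not whether it can tell the situations apart.

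**How much the by-arm count can show.** In the second situation the standard error of the difference is √(0.309 × 0.691/n₁ + 0.159 × 0.841/n₂):
- 67:33: √(0.00319 + 0.00405) = 0.085
- 33:17: √(0.00647 + 0.00787) = 0.120
- 14:7 (two METRA groups of 7): √(0.01525 + 0.01910) = 0.185

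A 15-point gap is under two standard errors at full size and under one at 14:7.

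**Why not a fixed between-arm trigger.** Take a trigger of METRA at least 15 points above TAU. At 67:33 it detects a 0.5 SD METRA-specific rise in 49% of trials and a 0.8 SD rise in 89%. With no METRA harm and background worsening of 0, 0.3 and 0.5 SD, it is met on at least one of two scales at two visits with these probabilities (20,000 simulated trials; correlation 0.5 across visits and across scales, 0.25 for a different scale and visit):
- 67:33: 7%, 14%, 19%
- 33:17: 30%, 39%, 41%
- 14:7: 40%, 49%, 53%

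A fixed trigger would thus call many needless reviews early on and still miss moderate harm.

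**The case against.** The strongest reply is that facilitators only inform and a body decides. That body can weigh context, including the insecurity. Adverse effects reach the Chief Investigators at once and the ethics and steering committees monthly, and {22} does not restrict this to METRA. High suicidality is excluded and referral is planned. Judgement without a formal boundary is normal in a small psychosocial trial. All this stands, and it lowers the weight of the point. It does not put a TAU figure in front of the body: {11b} names the facilitators' reports as the basis, and the adverse-effect list has neither a score definition nor an arm split.

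A second reply is that a one-arm count is the more sensitive alarm. That is also fair: the 25% cut is met in 87% of trials with a 0.5 SD METRA-specific rise, against 49% for a 15-point by-arm trigger. But it is met just as often when the same rise comes from the setting. Facilitator reports should therefore be kept and the by-arm counts added to them.

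Some stronger readings are tempting, and the documents do not support them:
- That symptoms cannot be compared with TAU during the trial. The scores exist in both arms; only their use is unplanned.
- That the distress limb is already met at entry because "elevated psychological distress is defined as >30 on the Persian Child Revised Impact of Event Scale-13" ({10}). Distress arising during sessions is the more natural meaning.
- That no committee charter exists. {21a} rules out a data monitoring committee and is silent on the steering committee's terms of reference.
- That the absence of values for the word significant is itself the fault. Alone, it is missing detail.

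Finally, {11b} says the facilitators, not the METRA facilitators. Limiting them to METRA is an inference, though no others are described.

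**Conclusion.** The point holds in a limited form. As {11b} is written, harm would be judged on unblinded impressions from what is in effect one arm, while blinded scores from both arms are collected at the right visits and left unused for this purpose. Under the stated assumptions, 0.5 SD of background worsening and 0.5 SD of METRA harm give the same METRA picture (31% risen), and only the TAU share (31% or 16%) distinguishes them. The text-based finding does not depend on those assumptions; the size does. The correlation, the 1 SD cut, 100 girls recruited and all assessed, and independence between girls in a group are assumptions.

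The linear mixed model or GEE analysis in {20a} is not affected: no estimate, test or significance level changes. A reader might infer that a numerical stopping boundary is required. The calculations argue against one at this sample size. The change is worth considering; it is not a condition for a valid trial.

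**What to change.** Reword {11b}, and adjust {21a} to match:

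1. Name the independent members of the Trial Steering Committee as the deciding body.
2. Keep the facilitator reports and the {22} adverse-effect lists, and add a cumulative, descriptive summary by arm from the post-Module 1 and post-Module 2 scores: number assessed; number not assessed, with reasons; and number whose CRIES-13 or MFQ short-form score rose by more than a pre-stated amount, for example 1 baseline SD.
3. Have it prepared by a team member who is neither an assessor nor a facilitator, so that assessors stay blind.
4. State that the members use judgement: no automatic stop, no fixed between-arm trigger and no efficacy test, so the significance level is untouched.
5. Turn the distress limb into an individual rule: pause that girl's sessions and refer her, on a report from a facilitator, an assessor or a TAU provider.
6. Say in the text that early summaries rest on small numbers, need cautious reading, and can miss a harm of about 0.5 SD.

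**Cost.** There are no new measures, visits or participants. The change needs prompt data entry between modules, which is a real burden where assessments had to be kept short for safety, and one existing team member unblinded to these counts. The members will also see noisy differences and will sometimes discuss one that means nothing.

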### **Strategies to improve adherence to interventions {11c}**

Group facilitators will be trained and receive supervision. A random 25% of the audio-recorded treatment sessions will be rated for manual adherence. To reduce group contamination, participants will be requested to not discuss treatment with others.

### **Relevant concomitant care permitted or prohibited during the trial {11d}**

N/A

### **Provisions for post-trial care {30}**

Referrals to local mental health services and NGOs will be made for participants requiring further psychological care.

### **Outcomes {12}**

*Primary Outcomes:* self-reported symptoms of PTSD (Child Outcomes Research Consortium, 2019) and depression (Neshat-Doost et al., 2006). We will assess statistical significance of change in the levels of PTSD and depression symptoms in the intervention and control groups.

*Secondary Outcomes:* Afghan-specific symptoms (Miller et al., 2006; Rasmussen et al., 2014); anxiety (Reynolds & Richmond, 1978); and internalising/externalising problems (Alavi et al., 2009).

*Qualitative data:* Interviews with adolescents in the METRA arm of the trial will be conducted to examine appropriateness and feasibility of METRA.

The measures and interviews will be conducted in Pashto and Dari.

[figure not shown]

Figure 1: Flowchart of participant recruitment and assessment

#### **Sample size {14}**

A priori power analysis was undertaken using G\*Power for depression and PTSD outcomes to detect a small to moderate interaction effect ( $f=0.15$ ) [18,33] between group (intervention, control) and time (pre-test, post-test) at an alpha-level of 0.05. A sample size of 90 participants would achieve power  $>0.80$ . The sample size estimate was re-adjusted to allow for attrition and we aim to recruit  $>100$  participants.

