**Statistical methods****Statistical methods for primary and secondary outcomes {20a}**

All primary analyses will be on intent-to-treat principle, with all randomized participants analyzed in their allocation condition.

Objective 1 will be examined using linear mixed effects models with intervention type, time, and intervention by time interaction as fixed factors (CHANGE 6: This was changed to generalized estimating equations following reviewer feedback. However, the results were the similar when using linear mixed effects models). Repeated assessments of individuals will be modelled as random intercept. Of primary interest will be the intervention by time interaction, which will compare the levels of change over time in outcomes of the METRA and TAU groups. Levels of significance will be set at  $\alpha < .05$  and hypothesis tests will be 2-sided. Objective 2: Thematic analysis of qualitative data (Atkins et al., 2017; Braun & Clark, 2006; Marks & Yardley, 2004) will assess feasibility and appropriateness.

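### The N=90 calculation has 0.80 power for a between-arm difference in change of about 0.60 SD, so calling the target effect small to moderate overstates the trial's sensitivity

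*Supplement*

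**What the plan says.** All references are to Version 2 (September 2021).

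- Sample size {14}: a G*Power calculation for the depression and PTSD outcomes was made "to detect a small to moderate interaction effect", given as f=0.15. The interaction is the one "between group (intervention, control) and time (pre-test, post-test"), and the test is made "at an alpha-level of 0.05". On the number needed, the section says: "A sample size of 90 participants would achieve power" above 0.80. The estimate was then "re-adjusted to allow for attrition and we aim to recruit" more than 100 participants.
- Statistical methods {20a}: the main contrast sets METRA against TAU: "Of primary interest will be the intervention by time interaction, which will compare the levels of change over time in outcomes of the METRA and" (the sentence ends by naming the comparator). The section adds that "hypothesis tests will be 2-sided".
- Sequence generation {16a}: allocation is 2:1 to METRA or TAU, and the section states that this should not affect power.

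The plan gives no pre-post correlation, no definition of f, no SD, no standardised difference d, no raw-score difference and no attrition rate.

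**The concern.** An f for a group-by-time interaction can be defined in more than one way, and the same number can then stand for different treatment effects. On the familiar scale where f is half of d, 0.15 lies between the usual benchmarks for small (0.10) and medium (0.25), so the plan's label looks natural. The routine that yields 90 participants uses another definition, under which 0.15 is a much larger treatment difference.

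The sample-size section is the plan's only statement of what the trial can detect. Taken at face value, it invites a reader to treat a non-significant interaction on PTSD or depression as evidence against a modest benefit. The calculation gives little protection against missing one. For a low-intensity intervention proposed for scale-up, modest effects are of interest.

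**Working it through.** **Inputs.** From Sample size {14}: f=0.15, two groups, two time points, alpha 0.05, N=90, power above 0.80. From {20a}: two-sided tests. From {16a}: 2:1 allocation. Assumed because not stated: pre-post correlation rho.

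**1. Reproduce the plan's figure.** For a within-between interaction with m=2 time points, use a noncentral F with 1 and N−2 degrees of freedom and

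lambda = N × f² × m / (1 − rho).

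With N=90, f=0.15 and rho=0.5: lambda = 90 × 0.0225 × 2 / 0.5 = 8.1, and power is 0.804. N=89 gives 0.799, so 90 is the smallest N that reaches 0.80. Smallest even N at other correlations:

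| rho | 0 | 0.3 | 0.5 | 0.6 | 0.7 | 0.8 |
|---|---|---|---|---|---|---|
| N for 0.80 | 178 | 126 | 90 | 72 | 56 | 38 |

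Among these, only rho=0.5 returns 90. If f is instead defined so that lambda = N × f² = 2.025, power at N=90 is 0.291 and about 350 participants are needed, so that definition does not produce the plan's figure.

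**2. Translate f into a treatment difference.** Take cell means of 0, 0 (TAU, pre and post) and 0, delta (METRA), with a single-occasion SD of 1. After removing the group and time effects, the four interaction terms are ±delta/4. In this routine f is their root mean square divided by the SD, so f = delta/4 and delta = 4 × 0.15 = 0.60 SD. This step does not depend on rho.

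**3. Check on change scores.** The SD of change is SD × √(2(1 − rho)), which equals one SD at rho=0.5. For a two-arm comparison of change, lambda = delta² × n1·n2/(n1+n2). With 45 per arm and delta=0.60: 0.36 × 22.5 = 8.1, the same as in step 1. A simulation of 50,000 trials gave power 0.803 at 0.60 SD and 0.290 at 0.30 SD.

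**4. Power at other differences (45/45, rho=0.5).**

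| Difference in change (SD) | 0.20 | 0.30 | 0.40 | 0.50 | 0.60 |
|---|---|---|---|---|---|
| Power | 0.16 | 0.29 | 0.47 | 0.65 | 0.80 |

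The 0.30 column is a translation made here from f = d/2 (d = 2 × 0.15). The plan states no d.

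**5. Sensitivity to the assumed correlation.** At 45/45 the smallest difference with 0.80 power is 0.597 SDs of change, or 0.597 × √(2(1 − rho)) single-occasion SDs.

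| Assumed rho | Detectable difference (SD) | Power at 0.30 SD |
|---|---|---|
| 0.3 | 0.71 | 0.22 |
| 0.5 | 0.60 | 0.29 |
| 0.7 | 0.46 | 0.44 |

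**6. The 2:1 allocation (rho=0.5).**

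- 60/30: n1·n2/(n1+n2) = 1800/90 = 20. At 0.60 SD, lambda = 0.36 × 20 = 7.2 and power is 0.756. At 0.30 SD power is 0.264. About 0.63 SD is needed for 0.80.
- 68/34 (102 analysed): 2312/102 = 22.67. At 0.60 SD, lambda = 8.16 and power is 0.81. At 0.30 SD power is 0.29. Since the target is just over 100 recruited, this case leaves almost nothing for attrition.

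**The case against.** The strongest reply is that nothing has been miscalculated: 90 follows from the f that was entered, and the label is attached to f, where 0.15 does lie between small and medium. That is right as far as it goes. A reader might infer that the sample-size arithmetic is wrong, or that the plan claims 0.80 power for d=0.30 and really has 0.29. The documents support neither, because the plan never states a d. What remains is that the label, read as a statement about treatment benefit, does not fit the 0.60 SD that this f stands for. That conclusion does not need d=0.30: at rho=0.5 no difference up to 0.50 SD reaches 0.80 power.

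Second, rho is inferred. The plan says only that power exceeds 0.80, which would also hold at a higher correlation. At an assumed rho of about 0.65 or more the detectable difference at N=90 is 0.50 SD or less (0.597 × √0.70 = 0.50), and the label would then be defensible. So it is too strong to say that the label and N=90 cannot both be true. Against that, correlations of 0.6 and 0.7 require 72 and 56 participants, so they do not explain the choice of 90. Whatever rho is, the f entered in this routine still corresponds to 0.60 SD.

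Third, these figures describe the plan's own two-occasion calculation. The trial has four assessments and a repeated-measures model, so they are not exact operating characteristics of the final analysis. It would also be wrong to call the trial informative only at 0.60 SD or more, since power at 0.50 SD is 0.65. Nor does the plan say that a null result will be read as excluding smaller effects; that is a risk of interpretation, not a stated intention.

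**Conclusion.** The point holds as a misdescription of sensitivity, not as an error in computing N. Given a within-between calculation, a pre-post correlation of 0.5 and 1:1 allocation, which together return exactly 90, the trial has 0.80 power for a between-arm difference in change of about 0.60 SD or more. That is above a medium effect (0.50) on the d scale. At 0.30 SD, the value to which f=0.15 would correspond on the half-of-d scale, a real benefit would be missed in about 7 trials of 10 (1 − 0.29 = 0.71). The detectable difference runs from 0.71 to 0.46 SD as the assumed correlation goes from 0.3 to 0.7. The 2:1 ratio moves it to about 0.63 SD for 90 analysed, where power at 0.60 SD is 0.756 rather than above 0.80. About 102 analysed restores 0.81 at 0.60 SD and does nothing material for smaller effects.

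**What to change.** In Sample size {14}:

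- Replace the small-to-moderate label with the detectable between-arm difference in pre-post change in SD units, and state the pre-post correlation and the definition of f. If the inferred settings are confirmed, wording such as this would do: with 90 analysed, 1:1 allocation and a pre-post correlation of 0.5, power is 0.80 for a difference in change of 0.60 SD.
- Give the same statement for the 2:1 allocation: about 0.63 SD for 0.80 power with 60/30, or power 0.81 at 0.60 SD with about 102 analysed. If the authors used another correlation or routine, they should state it and the matching figures.

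In Statistical methods {20a}, add that the group-by-time interaction will be reported with its confidence interval in SD units, and that a non-significant result will not be taken to exclude small-to-moderate effects.

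Keep the sample size. The change is wording and one reporting commitment, with no extra participants or data. The cost is a less favourable stated detectable effect.
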